## Abstract

**Introduction:** Rheumatoid arthritis (RA) is a globally challenging and refractory autoimmune disease, constituting a serious menace to human health. RA is characterized by recurrent pain and is difficult to resolve, necessitating prolonged medication for control. Yishen Tongbi decoction is a traditional Chinese herbal compound prescribed for treating RA. We have completed a 3-year RCT study that confirmed the clinical efficacy of Yishen Tongbi decoction for RA. Notably, we observed a faster clinical remission rate compared to MTX by week 4 of treatment. In our forthcoming study, we intend to conduct a comprehensive assessment of the efficacy and safety of Yishen Tongbi decoction in the real-world treatment of RA through a prospective study.

**Methods and analysis:** This prospective, multicenter, real-world observational study will be conducted at two designated centers in China from October 2023 to August 2025. The study will include 324 patients with active rheumatoid arthritis. One group will receive Yishen Tongbi decoction combined with conventional synthetic disease-modifying antirheumatic drugs (csDMARDs). The other group will receive standard treatment. Standard treatment can be further divided into subgroups: csDMARDs, targeted synthetic disease-modifying antirheumatic drugs (tsDMARDs), and biologic disease-modifying antirheumatic drugs (bDMARDs). In each group, the number of tender joints, number of swollen joints, pain score, patient global assessment, physician global assessment, disease activity index (DAS28-ESR or DAS28-CRP), clinical disease activity index (cDAI), simplified disease activity index (sDAI) and relevant laboratory data will be compared. Clinical indicators and disease activity of the patients will be assessed at baseline, week 4 and week 12 after the initiation of treatment. The primary outcome will be the American College of Rheumatology 20% improvement criteria (ACR20) attainment rate among patients at week 12 after treatment. Every adverse event will be reported.

**Ethics and dissemination:** This study has been approved by the Ethics Committee of the first affiliated Hospital of Guangzhou University of traditional Chinese Medicine (NO.K-2023-009). The results of the study will be published in national and international peer-reviewed journals and at scientific conferences. The researchers will inform participants and other RA patients of the results through health education.

**Clinical Trial Registration:**
https://www.chictr.org.cn/index.html, identifier ChiCTR2300076073

## Introduction

Rheumatoid arthritis (RA) is a systemic inflammatory autoimmune disease. Patients often exhibit joint pain and swelling, and disease progression can result in joint deformities and functional loss, significantly impairing physical function and quality of life (Smolen et al., 2018). It affects approximately 0.5%–1% of the global population, with an 8.2% increase in incidence between 1990 and 2017 (Gary et al., 2001; Finckh et al., 2022). As a lifelong condition, RA has made remarkable progress in the study of its pathogenesis and pathological changes in recent years, alongside an expanded array of available medication choices (Smolen et al., 2023).

The clinical management of RA necessitates personalized drug selection, giving rise to a diverse array of treatment approaches and primary medications. Conventional synthetic disease-modifying antirheumatic drugs (csDMARDs) is first-line treatment for RA, with methotrexate (MTX) being the current standard treatment for RA. However, it usually takes 6–8 weeks or even longer to observe clinical improvement (Wang et al., 2018). The clinical advancement and utilization of biologic disease-modifying antirheumatic drugs (bDMARDs) and targeted synthetic disease-modifying antirheumatic drugs (tsDMARDs) introduce fresh prospects in the treatment of RA. However, the infection and tumor risks associated with their prolonged utilization require further assessment (Burmester et al., 2015; Tanaka, 2023). In recent years, several randomized controlled trials (RCTs) have indicated that combining traditional Chinese herbal medicine with Western medicine is superior to Western medicine alone, providing both better outcomes and fewer adverse reactions (Gong et al., 2021; Shen et al., 2021).

Yishen Tongbi decoction (YSTB) is an herbal formula consisting of six medicinal herbs, including *Tripterygium wilfordii* Hook.f [Celastraceae; *T. wilfordii radix et rhizoma*] (Kunming Shan Hai Tang) (THH), *Eucommia ulmoides* Oliv. [Eucommiaceae; *Eucommiae Cortex*] (Du Zhong), *Ligustrum lucidum* W.T.Aiton [Oleaceae; *Ligustri Lucidi Fructus*] (Nv Zhen Zi), *Eclipta prostrata* (L.) L. [Asteraceae; *Ecliptae Herba*] (Han Lian Cao), *Lycium barbarum* L. [Solanaceae; *Lycii Fructus*] (Gou Qi), and *Salvia miltiorrhiza* Bunge [Lamiaceae; *Salviae miltiorrhizae radix et rhizoma*] (Dan Shen). We analyzed the primary chemical constituents in the extracts and evaluated the quality of YSTB extracts using UPLC-Q-TOF-MS/MS (The chromatogram of YSTB is presented in Supplementary Material S1). It is protected by Patent No. ZL 2010110191532. X and has shown efficacy in treating RA over a decade of use. We have completed a 24-week double-blind, double-model, randomized controlled trial comparing the effectiveness and safety of YSTB with MTX for active RA. At week 4, the YSTB groups exhibited a significantly higher attainment of ACR20 and EULAR good or moderate responses, indicative of a more rapid therapeutic effect compared to MTX (Xu et al., 2023). In our animal experiments, we observed that YSTB possesses anti-inflammatory properties, inhibits synovial hyperplasia, and improves bone destruction (Hu et al., 2021; Jiao et al., 2023). Cell experiments revealed that YSTB could inhibit the activation and proliferation of ST486 cells (Burkitt’s lymphoma ST486 human B cells) and promote the apoptosis of ST486 cells (Hu et al., 2021). The Main components of YSTB is shown in Table 1.

**TABLE 1 T1:** Composition and action of Yishen Tongbi decoction.

Pinyin name	Full species name	Pharmacological effects	Toxicity	Doses (g)
Kunmingshanhaitang	*Tripterygium wilfordii* Hook.f. [Celastraceae; *Tripterygium wilfordii radix et rhizoma*]	Kunmingshanhaitang has strong anti-inflammatory and immunosuppressive effects, which can significantly improve joint swelling and pain and delay bone destruction in patients with RA Chatzidionysiou et al. (2017), Drosos et al. (2020), Yates et al. (2020), Fujii et al. (2024)	hepatotoxicity, nephrotoxicity, reproductive toxicity Ru et al. (2019)	25
Nvzhenzi	*Ligustrum lucidum* W.T.Aiton [Oleaceae; *Ligustri Lucidi Fructus*]	Nvzhenzi can improve bone metabolism and inhibit osteoclast differentiation so as to achieve the effect of anti-osteoporosis Du (2010)	NA Cao et al. (2023)	15
Duzhong	*Eucommia ulmoides* Oliv. [Eucommiaceae; *Eucommiae Cortex*]	Duzhong can inhibit the secretion of pro-inflammatory cytokines, promote the secretion of anti-inflammatory cytokines, inhibit the proliferation of synovial cells and delay the degradation of chondrocytes and bones Wei et al. (2014)	NA Huang et al. (2021)	15
Gouqi	*Lycium barbarum* L. [Solanaceae; *Lycii Fructus*]	Gouqi has immunomodulatory, anti-inflammatory and anti-osteoporotic effects in the treatment of RA Chen et al. (2018)	NA Yu et al. (2023)	15
Danshen	*Salvia miltiorrhiza* Bunge [Lamiaceae; *Salviae miltiorrhizae radix et rhizoma*]	Danshen has specific anti-inflammatory and anti-immune effects Zhao et al. (2014)	NA Meim et al. (2019)	15
Hanliancao	*Eclipta prostrata* (L.) L. [Asteraceae; *Ecliptae Herba*]	Hanliancao can inhibit the proliferation and differentiation of RAW264.7 osteoclasts Xie et al. (2015)	NA Timalsina and Devkota (2021)	15

The decoction was made in the following manner: (1) Mix an appropriate quantity of cold water with Tripterygium wilfordii Hook.f. (THH; 25 g) and an equivalent amount of cold water with Ligustrum lucidum W.T.Aiton (15 g), Eclipta prostrata (L.) L. (15 g), Eucommia ulmoides Oliv. (15 g), Lycium barbarum L. (15 g), and Salvia miltiorrhiza Bunge (15 g) in a casserole, allowing it to steep for 30 min. (2) Boil THH, in 10 volumes of water for 3.5 h. (3) Combine the infusion of the remaining five herbs with 8 volumes of water, adding it to the THH, decoction that has boiled for 3.5 h, and simmer them together for an additional 40 min. (4) Strain out the residue and consume 150 mL once a day, preferably warm after meals.

We intend to validate these findings in extensive real-world clinical practice, recognizing the greater complexity of RA treatment in real-life scenarios compared to clinical trials. For these reasons, we aim to conduct a prospective real-world observational study with more subgroup analysis that focuses not only on the impact of YSTB on clinical outcomes, but also on the comparison of different treatment schemes in the real world.

### Objective

Based on previous RCT studies on YSTB, we will initiate a prospective real-world study to comprehensively assess the efficacy and safety of YSTB in RA treatment. Subgroup analyses will be used to evaluate the clinical remission effectiveness in RA patients receiving various treatment strategies. Furthermore, we will assess whether the combination of YSTB can provide additional significant beneficial results on the basis of csDMARDs.

## Methods and analysis

### Study design

This study is a prospective, multicenter, real-world observational clinical trial conducted at two designated centers in China from October 2023 to August 2025. The study included a population of 324 patients with RA. Treatment schemes were determined by doctors based on individual patient conditions and preferences. One group will receive YSTB combined with csDMARDs, while the other group will receive bDMARDs/tsDMARDs combined with csDMARDs, or a combination of two csDMARDs. The study protocol has been approved by the Ethics Committee of the First Affiliated Hospital of Guangzhou University of Traditional Chinese Medicine (approval NO.K-2023-009) and registered with the Chinese Clinical Trial Registry (ChiCTR2300076073). The study flowchart is shown in Figure 1. The Standard Protocol Items: Recommendations for Interventional Trials (SPIRIT) figure is shown in Figure 2.

**FIGURE 1 F1:**
[figure not shown]
Flow diagram of the clinical trial. RA Rheumatoid arthritis, YSTB Yishen Tongbi decoction, standard treatment includes bDMARDs/tsDMARDs along with csDMARDs, or a combination of two csDMARDs.

**FIGURE 2 F2:**
[figure not shown]
SPIRIT figure showing time points for enrolment, interventions and assessment. *Laboratory examination includes complete blood count, rheumatoid factor, Anticyclic citrullinated peptide antibody, C-reactive protein, erythrocyte sedimentation rate, liver function tests (aspartate aminotransferase, alanine aminotransferase) and renal function (creatinine, urea). csDMARDs Conventional synthetic disease-modifying antirheumatic drugs, bDMARDs Biological disease-modifying antirheumatic drugs, tsDMARDs Targeted synthetic disease-modifying antirheumatic drugs, ACR20/50/70 improvement in American College of Rheumatology criteria of 20%/50%/70%, CDAI Clinical Disease Activity Index, DAS28 Disease Activity Score in 28 joints, MTX methotrexate, SDAI Simplified Disease Activity Index.

### Inclusion criteria

Subjects must meet all of the following requirements:1) Meet the 2010 American College of Rheumatology (ACR)/European League against Rheumatism classification criteria and have RA for at least 6 weeks2) Have received and maintained standard RA treatment for at least 4 weeks3) Assessed as patients with mild, moderate, or severe RA based on DAS28-ESR/DAS28-CRP criteria4) Provide signed informed consent form

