### Outcome measures

The researchers will collect clinical data from patients at baseline, as well as at week 4 and week 12 following the initiation of treatment. Every Adverse event will be reported in time. The primary outcome is the attainment rate of the American College of Rheumatology 20% improvement criteria (ACR20) attainment rate among patients at week 12. ACR20 includes the number of tender joints, the number of swollen joints, and the fulfillment of at least 3 out of the following 5 criteria: visual analog scale (VAS) for Pain, patient global assessment, physician global assessment, Health Assessment Questionnaire (HAQ), C-reactive protein (CRP) or erythrocyte sedimentation rate (ESR). The above observation indicators meet the proportion of patients whose improvement reached 20%.

The secondary outcome is at week 12, the percentage of patients achieving clinical remission (DAS28-ESR <2.6) or low disease activity (LDA,DAS28-ESR <3.2) with the combination of YSTB combined with csDMARDs. The proportion of patients achieving a ≥50% improvement in cDAI or cDAI ≤2.8; the proportion of patients achieving a ≥50% improvement in sDAI or sDAI ≤3.3; The proportion of patients achieving ACR70, ACR50, EULAR good or moderate response, and a normal Health Assessment Questionnaire Disability Index score (≤0.5); Cumulative duration of effective treatment during the double-blind period; Results of patients’ self-evaluation. Adverse event is defined as all symptoms, signs, disease or discomfort that occur or aggravate during the follow-up process, including abnormal liver function, leukopenia, gastrointestinal reactions, rashes, palpitations, *etc.*

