### Statistical analyses

Attempting to ensure equivalence in baseline characteristics of participants between the YSTB group and the conventional therapy group, a propensity score method will be performed. Variables involving age, sex, smoking history, BMI and other factors will be included into the logistic regression model to calculate a propensity score for each participant. Participants who used YSTB will be matched to those who receive conventional drugs alone based on the propensity score, using the greedy matching with a standard calliper width of 0.2 and without case replacement. Covariate balance of the matched cohort will be assessed using the mean standardized differences. When a |d| > 0.10, it is considered as an imbalance. Inverse probability of treatment weighting based on the propensity score will also be performed to evaluate the robustness of the matching results. Baseline demographic variables will be presented as means, medians, or percentages, and using Chi-square test, independent *t*-test, or Mann-Whitney *U* test, as appropriate. Outcomes of CDAI, SDAI, DAS-28, ACR20, ACR50, ACR70 will be analyzed by using Chi-square test and logistic regression. Odd ratios and 95% confidence intervals will be estimated. Subgroup analysis will be performed on age, gender, treatment regimens (CHM alone, conventional medication alone and the combination). All analysis will be tested with a two-sided alpha level of 0.05 except the logistic regression. For the missing data, the reasons why the data is missing will be analyzed, and multiple imputation will be used.

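### Entry is by DAS28 category with no minimum joint count, so patients with a zero baseline tender or swollen count are eligible although ACR20 is undefined or unattainable for them

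*Protocol article*

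**What the plan says.** The Inclusion criteria section of the protocol article opens with "Subjects must meet all of the following requirements" and lists four items. Only the third concerns current disease activity: "Assessed as patients with mild, moderate, or severe RA based on DAS28-ESR/DAS28-CRP criteria". The second requires earlier therapy: "Have received and maintained standard RA treatment for at least 4 weeks". Neither the inclusion nor the exclusion list sets a tender or swollen joint minimum. The Abstract and Discussion call the disease active but do not tie that word to a joint count.

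Under Outcome measures, the primary outcome is the ACR20 rate at week 12, described as follows: "ACR20 includes the number of tender joints, the number of swollen joints, and the fulfillment of at least 3 out of the following 5 criteria". The two joint counts thus stand outside the three-of-five set, and the section sets the improvement threshold at 20%. The same section uses DAS28-ESR cut-offs of 2.6 for remission and 3.2 for low disease activity.

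Timeline of visits shows that joint status is recorded at baseline. Study design leaves the choice of treatment to the doctor, according to the patient's condition and preference.

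**The concern.** The entry rule and the primary endpoint measure different things. DAS28 is a weighted sum of joint counts, an inflammatory marker and the patient's global rating, so the last two can carry a patient over the threshold with no swollen joint, or with no affected joint at all. ACR20 requires a relative fall in each joint count, and no relative fall exists from zero. At least four weeks of maintained treatment before entry makes suppressed counts at baseline plausible.

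If such patients enter the primary comparison as automatic non-responders, both response rates are pulled down and the difference shrinks. If doctors' treatment choices track joint involvement, the share of such patients may differ between the groups, and the contrast may then be biased as well as diluted.

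**Working it through.** **1. The plan's own sample size.** Inputs from Sample size estimation: ACR20 of 87% versus 74%, two-sided alpha 0.05, power 0.80, total 324. The allocation ratio is not stated; 1:1 (162 per group) is assumed.

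- Pooled normal approximation: n = [1.960·√(2·0.805·0.195) + 0.842·√(0.87·0.13 + 0.74·0.26)]² / 0.13², which is 145 per group, 290 in total.
- With continuity correction: 160 per group, 320 in total.
- 290 inflated for an assumed 10% dropout: 145/0.9, rounded up, is 162 per group, 324 in total.

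The figure of 324 is therefore reproducible and is not in dispute. Power at 162 per group without continuity correction is 84.3%.

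**2. Does the entry rule admit zero counts?** The standard formula is used; its coefficients are an assumption because the article does not print them:

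DAS28-ESR = 0.56·√TJC + 0.28·√SJC + 0.70·ln(ESR) + 0.014·GH

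| TJC | SJC | ESR | GH | DAS28-ESR |
|---|---|---|---|---|
| 4 | 0 | 30 | 50 | 1.12 + 0 + 2.38 + 0.70 = 4.20 |
| 10 | 0 | 40 | 60 | 1.77 + 0 + 2.58 + 0.84 = 5.19 |
| 0 | 2 | 30 | 50 | 0 + 0.40 + 2.38 + 0.70 = 3.48 |
| 0 | 0 | 30 | 40 | 0 + 0 + 2.38 + 0.56 = 2.94 |
| 0 | 0 | 40 | 50 | 0 + 0 + 2.58 + 0.70 = 3.28 |

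All five exceed the article's remission cut-off of 2.6, and four exceed 3.2. Removing patients with low disease activity would therefore not close the gap.

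**3. What ACR20 does with a zero baseline.** Relative improvement is (baseline − week 12)/baseline. With baseline 0 and week-12 count x, this is (0 − x)/0: undefined, and never a demonstrable 20% reduction. Read plainly, the joint-count condition is not met.

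**4. Illustrative effect on power.** Let f be the share of patients with a zero baseline count. The article gives no value, so f is varied. Assumptions: 162 per group, equal f in both groups, and planning rates that contain no such patients. Scored as non-responders, the rates become 0.87(1 − f) and 0.74(1 − f). Excluded, the rates stay the same and n falls to 162(1 − f), rounded down.

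| f | Rates if non-responders | Power if non-responders | n per group if excluded | Power if excluded |
|---|---|---|---|---|
| 0 | 87.0% v 74.0% | 84.3% | 162 | 84.3% |
| 5% | 82.7% v 70.3% | 74.8% | 153 | 82.2% |
| 10% | 78.3% v 66.6% | 65.6% | 145 | 80.1% |
| 20% | 69.6% v 59.2% | 49.8% | 129 | 75.3% |

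**5. Unequal shares.** As a crude, unadjusted example with no true effect (74% in both groups), f of 5% in one group and 15% in the other gives 0.74·0.95 − 0.74·0.85 = 0.703 − 0.629 = 7.4 percentage points. The variables that Statistical analyses names for the propensity score are age, sex, smoking history and BMI, followed by an open reference to other factors. Joint counts are not named.

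**The case against.** The strongest reply has several parts.

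- **Scoring is an analysis-plan matter.** How a zero baseline enters a percent-change endpoint is a derivation rule that a protocol may leave to the analysis plan. This stands, and the absence of such a rule is not the point made here. An analysis plan can score these patients but cannot change who is enrolled, and the inclusion list is presented as complete.
- **Breadth is intended.** The Discussion names strict eligibility as a weakness of the earlier randomised trial. This is fair, but a floor of one joint narrows the population little, and a broad population still needs a primary endpoint that its members can reach.
- **The numbers rest on assumptions.** This stands. The share f is unknown, 1:1 groups are assumed, and the planning rates may already include such patients.
- **Adjustment is planned.** Matching, a balance check and weighting could remove an imbalance, and the open covariate list may include joint counts. The 7.4-point figure ignores all of this and shows only a mechanism.
- **The joint set may differ.** The examples use 28-joint counts. The article does not say which set ACR20 uses; on a wider set, fewer patients would have a zero count.

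A reader might infer that ACR20 simply cannot be computed for these patients. That goes too far, because a plain reading scores them as non-responders. A reader might also infer that their response would be filled in under "For the missing data, the reasons why the data is missing will be analyzed, and multiple imputation will be used". The article does not support this: a recorded count of zero is observed, not missing.

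**Conclusion.** The mismatch holds. Followed exactly, the plan admits patients for whom the primary endpoint is undefined or unattainable and places them in the primary comparison. That such patients are eligible depends only on the standard DAS28 formula; how many there will be cannot be known from the article.

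The size is therefore conditional. Under the stated assumptions, scoring these patients as non-responders takes power below the planned 80% by f = 5% (75%) and to 66% at f = 10%. Excluding them costs far less. A reader might take the 50% power at f = 20%, or the 7.4-point difference, as an expected consequence; nothing in the article supports either as a forecast. Bias is a risk only if the shares differ and baseline joint counts are left unbalanced. This is a cheap improvement that should be made, not a flaw that invalidates the design.

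**What to change.** Add to inclusion criterion 3: at least one tender and at least one swollen joint at the baseline assessment, counted on the joint set used for ACR20. The exact floor is for the sponsor to choose. A floor of one makes the endpoint attainable but coarse: with one swollen joint the smallest possible reduction is 100%, with two it is 50%, and only from five does a one-joint change equal 20%.

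For patients already enrolled with a zero count, exclude them from the ACR20 comparison in both groups on that baseline fact alone, before matching, and report the number in each group. Naming baseline tender and swollen counts among the propensity variables would address the remaining risk of imbalance.

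The cost is one line of text. Joint counts are already taken at baseline, so no new data are needed. The downside is a few patients lost and a slightly narrower real-world population, to which the ACR20 result would then apply.

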### Sample size estimation

Based on previous study and physician experience (Xu et al., 2023), this study comprises two independent trials with comparative rates. Its objective is to explore whether there exists a disparity in the ACR20 response rate between the two groups after 12 weeks of treatment. The prior study conducted by our research group indicated that after 12 weeks of treatment, the ACR20 response rate was 87% for the YSTB combined with the MTX group, while it was 74% for the MTX group. Assuming *α* = 0.05 (two-tailed test) and achieving a power of (1-β) = 0.8, we utilized PASS 15 software to calculate sample sizes for the experimental and control groups, totaling 324 patients to be included.

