
Although RCT is the gold standard for evaluating the safety and effectiveness of interventions, it has some limitations, such as strict inclusion and exclusion criteria, relatively small sample size, poor external authenticity, and high difficulty and cost of implementation. Real-world study (RWS) is a continuation and supplement of RCT, which aims to evaluate the actual efficacy of interventions in the real diagnosis and treatment environment under a large sample size, emphasizing external authenticity, and is widely used in disease diagnosis and treatment, prognosis and etiological analysis. High-quality RWS can accelerate the approval of new drugs and new indications (Knottnerus and Tugwell, 2010) In addition, the previous RCT study is a single-center study, a total of 82 patients completed the trial, the sample size is small, the multicenter trial with larger sample size is needed to obtain more objective clinical data for verification. Based on the above two points, our research group plans to carry out real-world study on the treatment of active RA patients with YSTB, in order to provide high-quality evidence-based medicine for the treatment of RA with traditional Chinese medicine compound, and promote the research and development of new drugs with low toxicity and high efficiency against RA.

Our research also has some limitations. First of all, there are subjective indicators evaluated by patients and doctors in the study. Therefore, these results may be biased. We can only assume that doctors maintain relatively uniform evaluation criteria and patients need further guidance on how to correctly assess the disease. Secondly, due to various reasons, it may be difficult for patients to adhere to the 12-week study cycle, so it is necessary to strengthen follow-up and timely communication with patients to minimize the drop-out rate. After the completion of the trial, we hope to make a clear conclusion on the efficacy and safety of YSTB.

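### Patients with mild RA by DAS28 may enter, and some would already meet the secondary low-disease-activity or HAQ-DI outcome at baseline; these outcomes need a baseline condition

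*Protocol article*

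**What the plan says.** - **Entry (Inclusion criteria, items 2 and 3).** Patients must "Have received and maintained standard RA treatment for at least 4 weeks" and be "Assessed as patients with mild, moderate, or severe RA based on DAS28-ESR/DAS28-CRP criteria". No numeric boundary is given for any grade, and either DAS28 version may be used.
- **Population label (Abstract; Discussion).** The Abstract states "The study will include 324 patients with active rheumatoid arthritis", and the Discussion says "our research group plans to carry out real-world study on the treatment of active RA patients with YSTB". The word *active* is not defined.
- **Secondary outcomes (Outcome measures).** At week 12 the plan counts "the percentage of patients achieving clinical remission (DAS28-ESR <2.6) or low disease activity (LDA,DAS28-ESR <3.2"), and also the proportion with HAQ-DI at or below 0.5. Both are states at week 12, with no baseline condition.
- **Primary outcome (Outcome measures).** "The primary outcome is the attainment rate of the American College of Rheumatology 20% improvement criteria (ACR20") at week 12, a change from baseline.
- **Treatment choice and adjustment (Interventions; Statistical analyses).** The doctor chooses treatment after assessing the patient's condition. The propensity score names age, sex, smoking history and BMI and leaves room for unspecified other factors. Baseline DAS28 is not named. No outcome is restricted by baseline status.

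**The concern.** An outcome defined as a state at week 12 measures the effect of treatment only in patients who were not in that state at the start. Someone who enters below 3.2 and stays there is scored as a success without having changed. The four weeks or more of prior standard treatment required at entry make such patients plausible.

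Two consequences follow for these secondary outcomes:

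- **Dilution.** Patients already at the threshold add similar successes to both groups and pull the rates together. The Discussion hypothesises that the YSTB combination is not inferior to standard treatment, so a pull towards no difference favours that conclusion.
- **Possible bias.** Treatment is not randomised and follows the patient's condition, so the share of mild patients may differ between groups. If baseline DAS28 is left out of the propensity score, matching need not remove that difference.

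The Objective section sets out to evaluate clinical remission across treatment strategies, so these outcomes carry weight although they are secondary.

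**Working it through.** **1. The plan's own figure.** The sample size rests on ACR20 alone: "the ACR20 response rate was 87% for the YSTB combined with the MTX group, while it was 74% for the MTX group", two-sided alpha 0.05, power 0.80, total 324. Assuming 1:1 allocation, the mean rate is (0.87 + 0.74)/2 = 0.805.

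n per group = [1.96·√(2·0.805·0.195) + 0.8416·√(0.87·0.13 + 0.74·0.26)]² / 0.13² = 145, total 290.

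With continuity correction this becomes 160 per group, total 320. Alternatively, 290/(1 − 0.10) = 323 if 10% dropout is assumed. Either is close to 324. The present point does not depend on this figure.

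**2. Entry band against outcome threshold.** The only DAS28 cut-offs in the article are 2.6 (remission) and 3.2 (low disease activity).

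| Baseline DAS28-ESR | Grade (inferred) | Below 3.2 already? | Below 2.6 already? |
|---|---|---|---|
| 2.6 to <3.2 | mild | yes | no |
| 3.2 or more | moderate or severe | no | no |

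Entry may be graded on DAS28-CRP while the outcome uses DAS28-ESR. A patient graded mild on CRP could therefore be below 2.6 on ESR and meet the remission outcome at entry as well. No entry criterion concerns HAQ-DI, so a patient may also start at 0.5 or less.

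**3. Dilution with equal shares (illustration).** Assume week-12 rates of 50% and 35% among patients above 3.2 at entry, 162 per group (324/2), and that every patient entering below 3.2 stays there. With a share m of such patients in both groups:

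- rates: m + (1 − m)·0.50 and m + (1 − m)·0.35
- difference: (1 − m)·0.15

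| m | Rates | Difference | Power, all patients | Power, only those above 3.2 |
|---|---|---|---|---|
| 0 | 50.0% vs 35.0% | 15.0 points | 0.78 | 0.78 |
| 10% | 55.0% vs 41.5% | 13.5 points | 0.68 | 0.74 |
| 20% | 60.0% vs 48.0% | 12.0 points | 0.58 | 0.69 |
| 30% | 65.0% vs 54.5% | 10.5 points | 0.49 | 0.63 |

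The last column uses 162·(1 − m) per group at 50% vs 35%. If only 80% of mild patients stay below 3.2, the differences are unchanged and power over all patients is 0.78, 0.69, 0.58 and 0.47.

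The plan reports odds ratios, and these shrink too. At m = 0 the odds ratio is (0.50/0.50)/(0.35/0.65) = 1.86. At m = 20% it is (0.60/0.40)/(0.48/0.52) = 1.63.

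**4. Unequal shares (illustration).** Assume no treatment effect, 40% attainment among non-mild patients, 90% of mild patients staying below 3.2, and no adjustment.

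- 30% mild: 0.30·0.90 + 0.70·0.40 = 55.0%
- 15% mild: 0.15·0.90 + 0.85·0.40 = 47.5%

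The false difference is 7.5 points. In general it is (difference in shares)·(0.90 − 0.40), so shares of 20% and 15% give 2.5 points and equal shares give none.

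**The case against.** The case against a wider reading is strong, and most of it stands.

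- **The study's endpoint is not met at entry.** A reader might infer that it is. ACR20 needs improvement in tender and swollen joints and in three of five further items, so nobody meets it at baseline. Nor is it shown that mild patients make ACR20 easier to reach. Losing one joint satisfies one component only, and a patient with no swollen or no tender joints cannot show a 20% reduction there.
- **The mild band is inferred.** The article gives outcome thresholds but no entry cut-points. The reading is natural, yet the authors may intend another boundary. If so, the text has to say so.
- **No outright contradiction with *active RA* is shown.** The criterion omits remission, so *active* could mean not in remission. Broad entry also suits a study that presents strict eligibility as a limitation of randomised trials. The wording needs reconciling.
- **Bias is not established.** The covariate list is open, and a balance check at a standardised difference of 0.10 is planned. Baseline DAS28 may be among the other factors.
- **Denominators for secondary outcomes are often left to an analysis plan**, and none is shown here. This limits the weight of the point. However, the entry rule and the outcome definitions are both stated in the article, and followed as written they score patients as successes without any change.

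**Conclusion.** The point holds for secondary outcomes only. As written, a patient entering at DAS28-ESR 2.6 to below 3.2 counts towards low disease activity at week 12 without improving, and a patient entering with HAQ-DI of 0.5 or less counts likewise. Remission at below 2.6 is exposed mainly through the mix of DAS28 versions.

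Dilution follows whenever such patients are enrolled and mostly stay where they are. Bias is conditional on unequal shares that the propensity score fails to remove.

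The size cannot be determined, because the share of mild patients is not given. The 12-point and 7.5-point figures are illustrations on assumed rates, and the latter also assumes 30% against 15% mild and no adjustment.

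A reader might go further and conclude that the primary ACR20 set should exclude mild patients. The documents do not support that. If 20% were mild, 324·0.80 = 259 would remain, fewer than the 290 needed for 80% power at 87% against 74%. Removing patients after matching would also break matched pairs.

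**What to change.** 1. Analyse low disease activity, remission and HAQ-DI of 0.5 or less among patients who do not meet the respective cut-off at baseline. Apply the propensity matching or weighting within that set, so that pairs are formed after the restriction.
2. Name baseline DAS28 as a propensity-score variable.
3. Use DAS28-ESR both to classify baseline status and to define the outcome.
4. State the cut-points behind mild, moderate and severe, and reconcile *mild* in the Inclusion criteria with *active RA* in the Abstract and Discussion.
5. Keep the primary ACR20 set unrestricted. Report ACR20 without patients below 3.2 at baseline as a sensitivity analysis only.

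The cost is wording and smaller denominators for these secondary outcomes. No new data are needed: Timeline of visits already lists disease activity, laboratory tests and health questionnaires at baseline. In the illustration with 20% mild, restriction leaves about 130 per group (162·0.80) with power 0.69, against 0.58 when all 162 are kept.
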